### Sample size calculation

GM is the most studied biomarker for the diagnosis of IPA among our candidate signatures; therefore, the sample size calculation is based on the diagnostic accuracy of the sputum GM assay reported by previous studies. Receiver operating characteristics (ROC) curves show the trade-off between sensitivity and specificity, and the area under the curve (AUC) is considered as an overall index of accuracy for quantitative biomarkers. The sample size estimation is based on AUC reported previously [27].

With 95% confidence (*α* = 0.05) to guarantee the marginal error of estimate (i.e. the difference between true AUC and its estimate) does not exceed from a pre-determined value of d = 0.09, and expecting an equal number of diseased and non-diseased cases, the required sample size for each group is:1$$ \mathrm{n}=\frac{{\mathrm{z}}_{\frac{\alpha }{2}}^2\ \mathrm{V}\left(\hat{\mathrm{AUC}}\right)}{d^2} $$

V($$ \widehat{\mathrm{AUC}} $$) denotes the variance of $$ \widehat{\mathrm{AUC}} $$ that is estimated parametrically based on binormal assumption [41, 42]. This binormal assumption is chosen because our study implements a four-category rating scheme (i.e. proven IPA, probable IPA, possible IPA and no IPA). $$ \mathrm{V}\left(\widehat{\mathrm{AUC}}\right) $$ is calculated as follows:2$$ \mathrm{V}\left(\widehat{\mathrm{AUC}}\right)=\left(0.0099\times {e}^{\raisebox{1ex}{$-{a}^2$}\!\left/ \!\raisebox{-1ex}{$2$}\right.}\right)\times \left(6{a}^2+16\right) $$

where a = *φ*^−1^(AUC) × 1.414 and *φ*^−1^ is the inverse of standard cumulative normal distribution. With a pre-specified AUC of 0.795 according to Kimura et al. [27], the required sample size for each group is 59 after above calculation. Therefore, we will recruit a minimum number of 118 participants with 59 controls (no IPA) and 59 cases (proven or probable IPA).

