### Statistical analysis

The data will be analysed with SPSS 22.0 software (IBM Corp, Armonk, NY, USA). Two analyses will be performed based on the IPA classification, one in which patients with possible IPA will be excluded in the calculation and a second analysis in which patients with possible IPA will be classified as not having IPA. Therefore, the comparisons and analyses will be (1) proven/probable IPA versus no IPA, and (2) proven/probable IPA versus possible/no IPA [43]. The sensitivity, specificity, negative predictive value (NPV), positive predictive value (PPV), and diagnostic odds ratio, including 95% confidence intervals, will be calculated for different biomarkers. ROC analysis will be performed and AUC (including 95% CI) and cut-off values will be established from the ROC curves for GM, RT-PCR, TAFC and bmGT. The McNemar χ^2^ test will be used to compare sensitivity, specificity, NPV, and PPV between different assays. The difference in hospital stay and the survival between possible or no IPA versus proven or probable IPA will be analysed with chi-square tests, and the relationships between the levels of biomarkers and the hospital stay and survival will be analysed via regression models. *P* < 0.05 will be defined as statistically significant.

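### PPV and NPV are to be taken straight from a sample targeted at 59 cases and 59 controls; if it is filled to that target, they do not describe inpatients with URD

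*Protocol article*

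**What the plan says.** The sample size section derives the number per group "expecting an equal number of diseased and non-diseased cases" and concludes that "we will recruit a minimum number of 118 participants with 59 controls (no IPA) and 59 cases (proven or probable IPA". The abstract likewise gives 118 as a lower bound.

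The statistical analysis section states that "negative predictive value (NPV), positive predictive value (PPV), and diagnostic odds ratio, including 95% confidence intervals, will be calculated for different biomarkers", and adds a McNemar comparison of PPV and NPV between assays. There are two analyses: "one in which patients with possible IPA will be excluded in the calculation", and a second that keeps these patients and counts them as not having IPA.

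The section on screening and recruitment describes a single stream. Admitted patients with respiratory disease are screened, recruited, and then classified. No quota is stated, and neither is consecutive enrolment. Nowhere does the article give an IPA prevalence for inpatients with URD, adjust the predictive values to one, or limit how they should be read.

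**The concern.** PPV and NPV are properties of a test at a given prevalence. If the case share is set by a recruitment target, the sample values describe that target and not the wards where the test would be used. The eligible population is broad: COPD, asthma, lung cancer, bronchiectasis, pneumonia, acute bronchitis and others. Nothing in the article suggests that half of these inpatients have IPA.

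A clinician reads PPV directly as the chance that a patient with a positive sputum test has the disease. With sensitivity and specificity held fixed, any true prevalence below the sample's case share makes the sample PPV too high. It also makes the sample NPV too low, unless sensitivity is 100%.

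**Working it through.** **The plan's own figure.** Inputs from the sample size section: "With 95% confidence", an error in the AUC that "does not exceed from a pre-determined value of d = 0.09", and "With a pre-specified AUC of 0.795".

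- a = z(0.795) × 1.414 = 1.165
- V = 0.0099 × exp(−a²/2) × (6a² + 16) = 0.1213
- n = 1.96² × 0.1213 / 0.09² = 57.5, rounded up to 58 per group

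The article states 59. The difference is one patient per group, so the figure is reproduced for practical purposes. At the planned minimum, the case share in analysis 1 is 59/118 = 50.0%.

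**Formulas.** With sensitivity Se, specificity Sp and case share p:

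- PPV = Se·p / [Se·p + (1 − Sp)(1 − p)]
- NPV = Sp(1 − p) / [Sp(1 − p) + (1 − Se)p]

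**Accuracy inputs.** Both pairs are cited in the article and serve as illustrations only. Sputum GM, 100%/62.2%, is from the Background and was obtained in haematological patients. BALF LFD, 77%/92%, is from the Discussion and was obtained in patients with URD.

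**Worked examples.**

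- GM at 50%: PPV = 0.5 / (0.5 + 0.378 × 0.5) = 72.6%
- GM at 10%: PPV = 0.1 / (0.1 + 0.378 × 0.9) = 22.7%
- LFD at 10%: PPV = 0.077 / (0.077 + 0.08 × 0.9) = 51.7%; NPV = 0.828 / (0.828 + 0.023) = 97.3%

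**Range.** The article gives no prevalence, so every row except 50% is an assumption.

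| Prevalence | GM PPV | GM NPV | LFD PPV | LFD NPV |
|---|---|---|---|---|
| 50% (target mix, analysis 1) | 72.6% | 100% | 90.6% | 80.0% |
| 30% | 53.1% | 100% | 80.5% | 90.3% |
| 20% | 39.8% | 100% | 70.6% | 94.1% |
| 10% | 22.7% | 100% | 51.7% | 97.3% |
| 5% | 12.2% | 100% | 33.6% | 98.7% |
| 2% | 5.1% | 100% | 16.4% | 99.5% |

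**Analysis 2.** Suppose m patients with possible IPA are added to 59 + 59 as non-cases. The case share is then 59/(118 + m). Specificity is held fixed here, which is a simplification, because patients with possible IPA may test positive more often than patients with no IPA.

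| m (assumed) | Case share | GM PPV | LFD PPV / NPV |
|---|---|---|---|
| 10 | 46.1% | 69.3% | 89.2 / 82.4% |
| 30 | 39.9% | 63.7% | 86.5 / 85.8% |
| 59 | 33.3% | 56.9% | 82.8 / 88.9% |
| 100 | 27.1% | 49.5% | 78.1 / 91.5% |

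The share falls below 50%, but it is still set by the 59/59 target and by how many possible cases happen to be enrolled.

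**Is the target mix compatible with consecutive enrolment?** To yield 59 cases, consecutive enrolment needs 59/0.10 = 590 patients at an assumed 10% share and 59/0.20 = 295 at 20%. A total close to 118 with 59 cases therefore implies either that the groups are filled to target or that the true share is near 50%.

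**Consecutive enrolment and analysis 1.** Dropping possible IPA from the denominator raises the case share whatever the enrolment. With equal numbers of cases, possible IPA and no IPA, for example, the share among those enrolled is 59/177 = 33.3%, but in analysis 1 it is 59/118 = 50.0%.

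**The case against.** The strongest reply is that the article does not impose a 1:1 quota. Equal groups are an input to the sample size formula, 118 is a minimum, and patients are classified only after recruitment. Recruiting until both minima are met could bring in far more than 59 patients without IPA. This stands: a reader might infer that the sample will be exactly half cases, but that holds only if the groups are filled to target. It does not remove the problem. The article does not say how 59 and 59 would arise from a single stream, and under consecutive enrolment analysis 1 would still have an inflated case share.

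A reader might also infer that possible IPA is left out throughout, so that all predictive values refer to 50% prevalence. The article does not support that. Only analysis 1 excludes these patients. Analysis 2 keeps all four classes, and under consecutive enrolment its raw PPV and NPV would describe the patients recruited.

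Two further limits stand. NPV is not understated in every case: with the cited sputum GM pair, sensitivity is 100% and NPV is 100% at every prevalence. And nothing in the article ranks PPV and NPV above the other measures. The sample size rests on the AUC, and PPV and NPV are listed alongside sensitivity, specificity and the diagnostic odds ratio.

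**Conclusion.** The point holds in a limited form. If recruitment is filled to the stated target, analysis 1 reports predictive values at about 50% prevalence and analysis 2 at a lower share that still depends on the target. Neither can be read as a value for inpatients with URD. On the cited accuracies, against an assumed 10% prevalence, PPV would be 73% instead of 23% for sputum GM and 91% instead of 52% for BALF LFD. LFD NPV would be 80% instead of 97%.

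The direction is certain for any prevalence below the sample's case share, with sensitivity and specificity held fixed and apart from the limiting cases of perfect sensitivity or specificity. The size in this population cannot be established, because the article gives no prevalence and the accuracy pairs are borrowed.

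It would be wrong to conclude that the trial's accuracy results are compromised. AUC, sensitivity, specificity and diagnostic odds ratio do not depend on the case:control ratio itself, and the stated sample size is reproduced to within one patient per group. The fault lies in how two of the planned measures are obtained and would be read.

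**What to change.** In the statistical analysis section:

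- Report sensitivity, specificity and likelihood ratios, with confidence intervals, as the sample results for each biomarker.
- Derive PPV and NPV by Bayes' rule over a stated range of prevalence. If enrolment is consecutive, include the observed IPA share among the consecutively recruited patients. The share among all screened eligible patients is not available as planned, because only recruited patients are classified.
- Label any raw sample PPV or NPV, and any comparison based on them, with the case share of the analysis concerned, and do not present them as values for inpatients with URD. With that label they need not be dropped.
- State whether enrolment is consecutive or the groups are filled to target, since this decides whether the sample share has any meaning outside the trial.

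The cost is some wording and one small table. Recruitment, assays, sample size and the AUC analysis do not change. The derived PPVs will probably look less favourable than the raw ones.

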### Statistical analysis

The data will be analysed with SPSS 22.0 software (IBM Corp, Armonk, NY, USA). Two analyses will be performed based on the IPA classification, one in which patients with possible IPA will be excluded in the calculation and a second analysis in which patients with possible IPA will be classified as not having IPA. Therefore, the comparisons and analyses will be (1) proven/probable IPA versus no IPA, and (2) proven/probable IPA versus possible/no IPA [43]. The sensitivity, specificity, negative predictive value (NPV), positive predictive value (PPV), and diagnostic odds ratio, including 95% confidence intervals, will be calculated for different biomarkers. ROC analysis will be performed and AUC (including 95% CI) and cut-off values will be established from the ROC curves for GM, RT-PCR, TAFC and bmGT. The McNemar χ^2^ test will be used to compare sensitivity, specificity, NPV, and PPV between different assays. The difference in hospital stay and the survival between possible or no IPA versus proven or probable IPA will be analysed with chi-square tests, and the relationships between the levels of biomarkers and the hospital stay and survival will be analysed via regression models. *P* < 0.05 will be defined as statistically significant.

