A variety of sample types and biomarkers have been explored and validated in the journey to seek mycological evidence for the diagnosis of IPA, and different methodologies and matching signatures have been investigated (Fig. 1). Direct mycological proof by culture is rarely feasible due to the low sensitivity and long turnaround time [18, 19]. Therefore, indirect tests that detect *Aspergillus*-related biomarkers, e.g., galactomannan (GM), in body fluids were developed, showed improved diagnostic performance and were included in the EORTC/MSG framework [17]. Serum biomarkers, in particular, *Aspergillus* DNA (*A*-DNA) and GM, have been intensively studied in haematological patients in the past two decades which exhibited good performance [20, 21]. However, these tests had lower sensitivity when applied in non-haematological patients [22, 23], probably because non-neutropenic patients tend to develop airway invasive aspergillosis instead of angioinvasive aspergillosis [24, 25]. This further indicates that biomarker detection based on organ specific samples may be associated with better diagnostic performance for IPA in non-neutropenic patients. Indeed, biomarker detection using bronchoalveolar lavage fluid (BALF) has been found to be associated with a higher diagnostic accuracy for IPA compared to serum in these patients [6–8, 26]. However, bronchoscopy is an invasive procedure and is not feasible for all patients in clinical practice. In contrast, induced sputum sampling is non-invasive, convenient and low cost and, if successful, often precludes the need for bronchoscopy. Sputum is expectorated from local sites of infection and can be used for microbiologic examinations, therefore, it has the potential to be used for biomarker determination in IPA.

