### Participants screening and recruitment

The study flowchart is shown in Fig. 2. Patients with respiratory diseases admitted into the hospital will be screened for inclusion and exclusion criteria for recruitment. The recruited patients will be subsequently assessed according to the clinical criteria shown in Table 2, namely newly-developed abnormalities in CT scan associated with IPA, for the classification of no IPA or suspected IPA groups. Patients without clinical criteria will be identified as no IPA. For patients with typical clinical criteria, those presenting histopathological or cytopathological evidence of *Aspergillus* hyphae from needle aspiration or biopsy specimen, or positive culture result for *Aspergillus* from a sample obtained by sterile procedure from the lung will be identified as proven IPA. If lung biopsy is not performed or negative result is generated, mycological examinations will be performed including sputum/BALF culture or serum/BALF GM tests to further classify patients as probable or possible IPA. Sample collection and testing will be required to be performed prior to antifungal treatment.

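### Specificity is never estimated separately in CT-suspected but unconfirmed patients: possible IPA is either excluded or pooled with controls who lack the CT signs

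*Protocol article*

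**What the plan says.** **Who becomes a control.** Under Participants screening and recruitment, recruited patients are assessed against the CT criteria "for the classification of no IPA or suspected IPA groups". Those without the CT criteria are labelled no IPA. Those with them are labelled proven if there is tissue or sterile-site evidence. Otherwise mycological tests (sputum or BALF culture, serum or BALF GM) sort them into probable or possible.

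**Definitions.** Table 3 (Diagnostic criteria) defines possible IPA as a host factor plus a clinical criterion, and no IPA as whatever is left over. Table 2 counts URD as a host factor. URD is also the first inclusion criterion (Study design).

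**Planned numbers.** The Sample size calculation plans for "59 controls (no IPA) and 59 cases (proven or probable IPA"). It gives no number for possible IPA.

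**Planned contrasts.** The Statistical analysis section states two: "the comparisons and analyses will be (1) proven/probable IPA versus no IPA, and (2) proven/probable IPA versus possible/no IPA". Possible IPA is left out of the first and counted as not having IPA in the second. ROC cut-offs for GM, RT-PCR, TAFC and bmGT are to come from the ROC analysis. The Discussion explains that the two analyses are meant to show how the possible-IPA group affects interpretation.

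**Motivation.** The Background says of induced sputum sampling that it, "if successful, often precludes the need for bronchoscopy".

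**The concern.** A diagnostic marker is most useful where the diagnosis is in doubt. Here the doubtful patients are those with a suggestive CT and no confirmation. Neither contrast isolates them. Analysis 1 compares CT-positive cases with controls who lack those CT signs. It cannot show whether a marker separates IPA from other causes of a dense lesion or cavity, and the enrolled diseases (lung cancer and bacterial pneumonia among them) may include such causes. Analysis 2 brings the doubtful patients in, but only blended with the controls.

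At stake is how far the specificity and cut-offs carry over. If marker levels differ between no IPA and possible IPA, a cut-off chosen in analysis 1 will have a different specificity in suspected patients, and the pooled figure from analysis 2 will describe neither group. A statement that sputum can spare bronchoscopy would then rest on a specificity not shown for the patients most likely to be sent for it.

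**Working it through.** **Step 1. The plan's own figure.** Inputs from the Sample size calculation: "With 95% confidence" (z = 1.96), a marginal error that "does not exceed from a pre-determined value of d = 0.09", "With a pre-specified AUC of 0.795", and "expecting an equal number of diseased and non-diseased cases".

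- a = 1.414 × Φ⁻¹(0.795) = 1.165
- V = 0.0099 × exp(−a²/2) × (6a² + 16) = 0.1213
- n = 1.96² × 0.1213 / 0.09² = 57.5, rounded up to 58 per group

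The stated 59 is within one patient of this (an AUC of 0.79 gives 58.3, so 59). The sample size is not in dispute. The planned precision applies to 59 cases against 59 no-IPA controls, that is, to analysis 1. Nothing is planned for possible IPA.

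**Step 2. Can a CT-positive patient be a control?**

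1. Every enrolled patient has URD (inclusion criterion).
2. URD is a sufficient host factor (Table 2).
3. A host factor plus one CT sign is at least possible IPA (Table 3).
4. So no patient meeting the CT criterion can be no IPA, and every no-IPA control lacks it.

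A CT-positive patient without proof or mycological evidence can therefore only be possible IPA.

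**Step 3. Where each group enters.**

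| Group | Analysis 1 | Analysis 2 |
|---|---|---|
| Proven/probable | case | case |
| Possible (CT-positive, unconfirmed) | excluded | control |
| No IPA (CT signs absent) | control | control |

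No stated contrast uses possible IPA alone as the comparator.

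**Step 4. What analysis 2 reports.** With 59 no-IPA controls of specificity s0 and m possible-IPA patients of specificity s1, at a common cut-off:

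pooled specificity = (59 × s0 + m × s1) / (59 + m)

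The documents give none of s0, s1 and m, so all three are assumed. With s0 = 0.90:

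| m | s1 = 0.50 | s1 = 0.60 | s1 = 0.70 | s1 = 0.90 |
|---|---|---|---|---|
| 10 | 0.842 | 0.857 | 0.871 | 0.900 |
| 20 | 0.799 | 0.824 | 0.849 | 0.900 |
| 30 | 0.765 | 0.799 | 0.833 | 0.900 |
| 59 | 0.700 | 0.750 | 0.800 | 0.900 |

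For example, m = 20 and s1 = 0.70 give (53.1 + 14.0)/79 = 0.849. Down a column the test is unchanged and only enrolment differs. The last column shows that with equal specificities there is no effect.

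**Step 5. Carrying a cut-off across.** Assume equal-variance binormal marker levels with the plan's AUC of 0.795. The Youden cut-off from analysis 1 lies at a/2 = 0.5825, where specificity in no IPA is Φ(0.5825) = 0.72. If levels in possible IPA are shifted by δ SD relative to no IPA, specificity there is Φ(0.5825 − δ), and the AUC of cases against possible IPA is Φ((1.165 − δ)/√2):

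| δ | specificity in possible IPA | AUC against possible IPA |
|---|---|---|
| 0 | 0.72 | 0.795 |
| 0.25 | 0.63 | 0.74 |
| 0.50 | 0.53 | 0.68 |
| 0.75 | 0.43 | 0.62 |

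A downward shift would reverse the sign: δ = −0.25 gives Φ(0.8325) = 0.80. The documents do not say which applies.

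**Step 6. Precision of a separate estimate.** The half-width is 1.96 × √(s1(1 − s1)/m). At s1 = 0.70 it is 0.28, 0.20, 0.16 and 0.12 for m = 10, 20, 30 and 59.

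**The case against.** The case for the plan has real force.

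- **Possible IPA is not ignored.** Analysis 2 puts these patients into its specificity and its ROC curve, and the Discussion gives a reason for running both analyses. A reader might infer that specificity and cut-offs are never estimated in suspected patients at all. The documents do not support that; they are never estimated *separately*. At a common cut-off, and for the LFD, which has none to choose, false positives in possible IPA can be recovered by subtracting the analysis 1 count from the analysis 2 count. This narrows the gap but does not close it: nothing says one cut-off will serve both analyses, and no such result is planned.
- **The controls are not trivially easy.** A reader might picture lesion-free patients. No IPA means only that the listed signs are absent. Inpatients with bronchiectasis, interstitial lung disease or pneumonia can have abnormal CTs and still qualify.
- **The target group is inferred.** The Background remark on bronchoscopy is about sputum sampling in general, and the stated population is URD. The link to CT-suspected patients comes from the screening section, which directs the mycological work-up, including BALF, to them. That makes the reading plausible, not stated.
- **No bias is demonstrated.** A reader might infer that specificity in suspected patients is known to be lower. No passage gives a stratum-specific figure.
- **Possible IPA is an imperfect comparator.** It may contain missed IPA (the Discussion cites serum GM sensitivity of 23.1–42% in non-haematological patients), which lowers apparent specificity. Colonised CT-positive patients with positive mycology are classed as probable and leave the denominator, which can raise it. It is tempting to call the possible-IPA figure a lower bound and analysis 1 an upper bound, but because these effects oppose each other, neither label is justified.

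An article may leave extra tables to an analysis plan, but this one states its comparisons as two, and the point concerns that stated choice.

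**Conclusion.** The structural point holds and follows from the protocol's own definitions. Controls lack the CT signs, CT-positive unconfirmed patients are dropped or pooled, and the analysis 2 specificity depends on an unplanned case mix. Its size and direction cannot be computed from the documents. On assumed specificities of 90% in no IPA and 50–70% in possible IPA, with 20 possible-IPA patients, analysis 2 would report about 80–85%, which is 15 to 30 points above the possible-IPA value (0.849 − 0.70 and 0.799 − 0.50). With equal specificities the gap is zero. The point does not show that the sample size is wrong or that either planned analysis is invalid. It is an inexpensive improvement that changes what the trial can conclude about suspected patients.

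**What to change.** In the Statistical analysis section, keep analyses 1 and 2 and add:

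1. Each marker's specificity with 95% CI, reported separately for no IPA and for possible IPA at the same cut-offs.
2. An exploratory AUC for proven/probable versus possible IPA within CT-positive patients. State that these categories differ mainly by mycology, which is related to the sputum markers, so this AUC partly measures agreement between related tests.
3. A sentence that neither specificity is a bound, with the two opposing reasons (missed IPA among possible, colonised patients among probable).
4. A sentence that no statement about sparing bronchoscopy will rest on analysis 1 alone.

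The cost is one table from data already collected. The drawbacks are a wide interval (about ±0.20 with 20 possible-IPA patients at 70%) and possibly a less favourable specificity.

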**Fig. 1 Fig1:**
[figure not shown]
Current biomarkers for the diagnosis of IPA using different sample types. Abbreviations: *A*-DNA = aspergillus DNA; bmGT = bis(methylthio)gliotoxin; GM = galactomannan; PCR = polymerase chain reaction; TAFC = triacetylfusarinine

We searched the literature using the terms “sputum”, “sputa”, “bronchial secretion”, “bronchial aspirate”, “respiratory sample” and “aspergillosis”, “*Aspergillus*” in Medline, EMBASE and PubMed databases up to the 20th of May 2017. Seven studies that assessed the GM assay with sputum samples were identified (Table 1), of which only the study by Kimura et al. [27] tested the efficacy of sputum GM for the diagnosis of IPA in haematological patients in a well-designed manner. The results of this study identified a sensitivity of 100% and a specificity of 62.2% for sputum GM at the cut-off value of 1.2 optical density index (ODI). However, the small sample size impeded the external validity of the study and the validation of an optimal cut-off value. Some studies have assessed *A*-DNA in sputum via the polymerase chain reaction (PCR) assay; however, these studies exclusively aimed at identifying the existence of *Aspergillus* in sputum rather than assessing the diagnostic performance for IPA [28–31]. Fraile et al. [32] and Chanzá et al. [33] intended to evaluate the sputum PCR assay for the diagnosis of IPA; however, diagnostic criteria according to the EORTC/MSG framework were not applied. Our study will use real-time PCR (RT-PCR) to detect sputum *A*-DNA for IPA in patients with URD diagnosed by the EORTC/MSG criteria.

**Table 1 Tab1:** Studies assessing sputum GM assay for various *Aspergillus* events

Author	Year	*Aspergillus* events	Underlying diseases	Sputum type
Kimura [27]	2009	IPA	HD	spontaneous/induced
Fraile [32]	2012	IPA^a^	not classified^b^	not reported
Delfino [34]	2012	AC	cystic fibrosis	not reported
Baxter [29]	2013	AC	cystic fibrosis	spontaneous
Baxter [28]	2013	ABPA	cystic fibrosis	spontaneous
Chanzá [33]	2014	IPA^a^	HD and NHD	not reported
Dhillon [35]	2016	ABPA	cystic fibrosis	not reported

*Abbreviations*, *ABPA* allergic bronchopulmonary aspergillosis, *AC Aspergillus* colonization, *HD* haematological disease, *IPA* invasive pulmonary aspergillosis, *NHD* non-haematological disease

^a^EORTC/MSG diagnostic criteria were not used.

^b^Patients recruited from Infectious, Pneumology, Oncology Services and Critical Care Unit, without specific underlying diseases classified.

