### *A*-DNA extraction and RT-PCR

Fungal DNA will be extracted from 1.5 mL of the sputum suspension with the commercial MycXtra fungal DNA extraction kit (Myconostica Limited, Manchester, UK), and *A*-DNA will be detected with the MycAssay *Aspergillus* kit (Myconostica Limited, Manchester, UK), according to the manufacturer’s instructions. PCR runs will be performed on a CFX Connect™ RT-PCR system (Bio-Rad, California, USA) by targeting a portion of the 18S ribosomal gene, in accordance with the detection kit protocol. Ten microliters of extracted DNA will be used in a final reaction volume of 25 μL. The PCR protocol is as follows: 10 mins at 94 °C; 10 s at 94 °C, 58 s at 57 °C, and 20 s at 72 °C for 40 cycles. The cycling threshold will be recorded and used for subsequent analysis, including the determination of an optimal cut-off value, based on which the sputum samples will be regarded as positive or negative for *Aspergillus* infection.

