RT-PCR is a precise approach to detect *A*-DNA, and it has been applied for serum and BALF samples even though there is a lack of standardized protocol. Several meta-analyses [21, 63–67] assessed the efficacy of PCR assays on these two sample types for the diagnosis of IPA in haematological patients. The results showed that BALF PCR had much higher sensitivity (approximately 90%) and specificity (> 90%) than serum (85% for sensitivity and 75% for specificity). Several studies [28, 29, 68, 69] used PCR to identify *Aspergillus* in sputum and showed that sputum PCR had higher sensitivity than routine fungal culture; however, this technique has not been applied in the diagnosis of IPA and will be addressed in our study.

Sputum is a type of sample that is viscous and heterogeneous. To accurately detect biomarkers in sputum plugs, a proper processing method is needed. Dithiothreitol (DDT) is a commonly used reagent to homogenize sputum before all kinds of constituents are examined, and it is recommended for the pre-treatment of viscous samples by guidelines [70]. Baxter et al. [28] processed sputum with DDT and sonication before performing a GM assay and the results showed excellent GM reproducibility and low interassay and intraassay coefficients of variation. However, Prattes et al. [71] examined the effect of DDT on a BALF GM assay and found conflicting results. GM levels in BALF were substantially decreased from 0.51 ODI to 0.01 ODI after pre-treatment with DTT, and the LFD assay in BALF was also dramatically affected. Although this study targeted BALF, it is likely that DTT might affect sputum GM and LFD detection. Therefore, to minimize the effect of DTT on these biomarker assays, we will pre-treat sputum samples with phosphate buffered saline, which is in accordance with the method by Kimura et al. [27].

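### Sputum cut-offs are tuned on the trial's own ROC curves and assessed in the same patients, so the cut-off-dependent accuracy figures are optimistic on average

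*Protocol article*

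**What the plan says.** Statistical analysis: "AUC (including 95% CI) and cut-off values will be established from the ROC curves for GM, RT-PCR, TAFC and bmGT". The same paragraph plans sensitivity, specificity, NPV, PPV and DOR, each with a 95% interval, for the biomarkers, and McNemar tests between assays.

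A-DNA extraction and RT-PCR: the cycling threshold will be used for "determination of an optimal cut-off value, based on which the sputum samples will be regarded as positive or negative". Here the derived cut-off is explicitly applied to the study's own samples. The Discussion adds that suitable cut-offs for the sputum biomarkers will be determined in this study.

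Other assays are treated differently. Under GM detection, serum and BALF GM have cut-offs fixed in advance (0.5 and 1.0 ODI). Under LFD performance, the device is read as line present or absent.

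The Background cites an external sputum GM cut-off, with "sensitivity of 100% and a specificity of 62.2% for sputum GM at the cut-off value of 1.2 optical density index", from a study of haematological patients. On sample handling the Discussion says "we will pre-treat sputum samples with phosphate buffered saline, which is in accordance with the method by" that same study. The 1.2 ODI value is not adopted.

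**The concern.** A cut-off picked because it separates these particular cases and controls well exploits their chance pattern as well as the real signal. Accuracy read off at that cut-off in the same patients is then, on average, better than the same cut-off would achieve in new patients. An ordinary binomial interval treats the cut-off as given, so it is centred too high and leaves out one source of variation.

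Two things are at stake. One is the sensitivity, specificity, PPV, NPV and DOR that clinicians would take from the trial for sputum GM, RT-PCR, TAFC and bmGT. The other is the McNemar comparison with assays whose positivity rule is not tuned (LFD, serum GM, BALF GM). There the tuned marker has an advantage that comes from the analysis and not from the assay.

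**Working it through.** **1. The plan's own figure.** The inputs are in Sample size calculation: "With 95% confidence" (z = 1.96), a margin of error that "does not exceed from a pre-determined value of d = 0.09", "With a pre-specified AUC of 0.795 according to" the earlier haematology study, and "expecting an equal number of diseased and non-diseased cases".

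- a = 1.414 × Φ⁻¹(0.795) = 1.165
- V = 0.0099 × exp(−a²/2) × (6a² + 16) = 0.1213
- n = 1.96² × 0.1213 / 0.09² = 57.5, rounded up to 58 per group

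The article states 59 per group. The difference of one patient is immaterial, and 59 + 59 is used below.

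**2. Simulation of the cut-off step.** From the article: 59 cases, 59 controls, AUC 0.795. Assumed, because the article does not say: the cut-off maximises Youden's J = sensitivity + specificity − 1 in the sample, and the marker is normal with equal variance in both groups, with means √2 × Φ⁻¹(AUC) apart. In each of 20,000 simulated trials the apparent accuracy at the chosen cut-off was compared with the true accuracy of that same cut-off in new patients.

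| Measure (AUC 0.795) | Apparent | True | Excess |
|---|---|---|---|
| Sensitivity | 76.2% | 72.1% | 4.1 points |
| Specificity | 73.3% | 70.1% | 3.2 points |
| J | 0.495 | 0.422 | 0.073 |
| PPV (50% prevalence) | 75.0% | 71.6% | 3.4 points |
| NPV (50% prevalence) | 76.5% | 72.4% | 4.1 points |
| DOR (geometric mean) | 9.9 | 6.8 | 9.9/6.8 = 1.46 |

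On medians, the DOR is 9.5 against 6.7, a ratio of 1.42. Apparent J exceeded true J in about 86% of trials, sensitivity did so in 79% and specificity in 72%.

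**3. Sensitivity to the assumptions.**

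| Scenario | Excess in J |
|---|---|
| AUC 0.70, 59 + 59 | 0.084 |
| AUC 0.90, 59 + 59 | 0.060 |
| AUC 0.795, 30 cases of 118 | 0.089 |
| AUC 0.795, 20 cases of 118 | 0.107 |
| AUC 0.795, 59 cases + 120 controls | about 0.064 |
| AUC 0.795, 100 + 100 | about 0.054 |
| Mostly undetectable in controls (assumed 2–10% of controls and 60–70% of cases detectable), 59 + 59 | about 0.02 |

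**4. Interval coverage.** With the tuned cut-off, the two nominal 95% Wilson intervals for sensitivity and specificity jointly cover the truth in about 85% of trials. The right comparator is not 95%: two independent 95% intervals jointly cover 0.95² = 90%, and with a fixed cut-off the simulation gives about 92%. The loss is about 7 points.

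**5. McNemar comparison.** Two markers were given the same true AUC of 0.795 and a within-group correlation of 0.5 (assumed), with 59 + 59 patients and 8,000 trials. One had a Youden cut-off from the sample and the other a cut-off fixed at the true optimum. The tuned marker was significantly better (P < 0.05, uncorrected χ² form) on sensitivity or specificity in 38% of trials, and the fixed one in 16%. At AUC 0.70 the figures were 51% and 26%. Part of both rates comes from the sample cut-off trading sensitivity against specificity. The asymmetry between them is the tilt. An exact or continuity-corrected test lowers both rates but leaves the asymmetry.

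**6. Does correction work?** In 600 simulated trials with the cut-off re-selected inside each bootstrap sample, apparent J 0.495 was corrected to 0.445 against a true 0.424. That removes (0.495 − 0.445)/(0.495 − 0.424) = 70% of the bias.

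**The case against.** **The AUC is sound.** A reader might infer that every accuracy figure for these markers is too good. The documents do not support that. The AUC is reported with its interval, is described as the overall index for quantitative biomarkers, and is the sole basis of the sample size. It needs no cut-off. This limits the point to the five cut-off-dependent measures.

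**A condensed article.** Internal validation is often left to a fuller plan, so its absence here is not the finding. Same-sample classification is explicit only for RT-PCR. Both statements are fair. What remains is the rule that the article does fix: sputum cut-offs come from this cohort's ROC curves, and no other source is given for GM, TAFC or bmGT.

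**The size is assumed.** The article names neither a selection rule nor a marker distribution. TAFC and bmGT were undetectable in the four pilot sputa without IPA, 118 is a minimum, and the second analysis adds possible-IPA patients to the controls. Each of these could reduce the bias. Fewer cases than planned would increase it.

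**The bias is small beside sampling error.** At n = 59 and 72% sensitivity the half-width is 1.96 × √(0.72 × 0.28/59) = 11 points, against a bias of 3 to 4. This stands and lowers the severity. The bias nevertheless has a known direction, and the intervals do not reflect it.

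**Deriving cut-offs is an aim, and 1.2 ODI comes from elsewhere.** One might argue that 1.2 ODI should be the primary cut-off. It comes from haematological patients, and this trial excludes haematological malignancy. A shared buffer does not establish a shared assay scale. It suits a secondary analysis only. Nor does the trial plainly repeat a fault it criticises: the Background blames the earlier study's small sample, not same-sample selection.

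**Conclusion.** The point holds for sensitivity, specificity, PPV, NPV and DOR of sputum GM, RT-PCR, TAFC and bmGT. Under a Youden cut-off, an equal-variance binormal marker, 59 + 59 patients and AUC 0.795:

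- sensitivity and specificity are each about 3 to 4 points too high;
- J is about 0.50 against 0.42;
- the DOR is about 40 to 45% too high;
- joint interval coverage is about 85% against about 92% with a fixed cut-off.

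These are averages under assumptions that the article does not state. A single trial can fall the other way, and markers mostly undetectable in controls may show much less bias. Comparisons with LFD, serum GM and BALF GM tilt toward the tuned markers.

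Two stronger readings are not supported. That the results will fail to reproduce elsewhere does not follow from an average bias of this size. That the AUC of the winning marker will be inflated by selection rests on a closing question in the Discussion about the strongest candidate, and no selection procedure is planned.

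Severity: should-fix.

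**What to change.** 1. State the rule by which each sputum cut-off is chosen.
2. Repeat that selection inside every bootstrap sample or cross-validation fold. Report optimism-corrected sensitivity, specificity, PPV, NPV and DOR, with intervals that include the selection step.
3. Label any uncorrected figure as apparent, and read McNemar comparisons of tuned with untuned assays in that light.
4. As a secondary analysis, report sputum GM accuracy at the published 1.2 ODI as an external cut-off, noting that it comes from haematological patients.

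The cost is some wording and programming, with no new patients or assays. The figures become slightly less favourable and the intervals wider. The correction is partial: in the check above it removed about 70% of the bias.
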